#### Secondary outcomes

Incidence of endoscopic recurrence with a Modified Rutgeerts score ≥i2b at 3 years follow‐up.Incidence of severe endoscopic recurrence (Modified Rutgeerts score ≥i3) at 3 years follow‐up.Clinician and patient‐reported symptomatic recurrence up to 3 years [31].Quality of life (EQ‐5D‐5L) [32] assessed at baseline, 6 weeks and 12 months post‐surgery.Surgical recurrence up to 3 years (clinician and patient reported).Radiological and surgical anastomotic leak as defined by the latest consensus [33]; other complications for each intervention assessed at the time of surgery, 6 weeks and 12 months post‐intervention.

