**FIGURE 1 codi70212-fig-0001:**
[figure not shown]
Study flowchart demonstrating participant journey through the trial from identification, enrolment, treatment allocation and follow‐up.

**TABLE 1 codi70212-tbl-0001:** Schedule of assessments during the study.

	Baseline	Operation	6 weeks	12 months (−6 to +3 months)	Study end (up to 5 years)
Eligibility assessment	X	X			
Consent	X				
Medical history	X				
Concomitant medications	X		X	X	X
Demographics	X				
IBD‐Control	X		X	X	
CDAI	X		X	X	
EQ‐5D	X		X	X	
Randomisation		X			
Mesenteric disease activity index		X			
Adverse events		X	X	X	
Colonoscopy				X	X (via note review)
Blood samples	X			X	
Mucosal/mesenteric biopsies		X		X	
Surgical recurrence				X	X (via note review)

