### Sample size

The primary outcome will be the time to endoscopic recurrence (ER) post‐randomisation (Modified Rutgeerts score ≥ i2). All participants will be followed up for a minimum of 6 months post‐randomisation and up to a maximum of 3 years. The best existing data indicates ER rates of approximately 65% on conventional surgery and 24% on Kono‐S surgery at 12 months [34]. Other published data on the rate of endoscopic recurrence after conventional surgery varies from 58% to 93% [28, 35, 36, 37]. The systematic review unfortunately found no published data on the ER rates after close or extended mesenteric resection [16]. In a survey of 34 surgeons, 71% were persuaded to change practice based on a reduction in endoscopic recurrence to 30% or less after 12 months.

The sample size calculation for the 2 × 2 factorial design assumes: 90% power; 5% (two‐sided) significance level; and estimated reduction in 1‐year endoscopic recurrence rates from 52.5% to 32.5%. Using the Freedman method a total of 112 recurrences are required [38]. After accounting for surgeon effects (assuming each of 12 sites would have 2 surgeons, an ICC of 0.01 and 15 patients per surgeon) and an attrition rate of 3%, the target sample size is 154 per group for each comparison.

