### Recruitment

Potential participants will be discussed at MDT meetings and identified at the time of pre‐operative assessment before the day of surgery. Potential participants will be approached either at their clinic visit prior to surgery or pre‐operative assessment. The study will be run nationally within the United Kingdom across up to 27 centres, recruiting one participant per month over a maximum of 45 months.

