### Data collection

Baseline data will be collected by a research nurse or clinician using specific case report forms (Table 1). Participants will be given a diary to complete 7 days prior to the day of surgery to enable the Crohn's Disease Activity Index (CDAI) to be calculated (Appendix 2). Operative details will be recorded by the operating surgeon. Six‐week and 6‐ to 12‐month follow‐up data will be collected by a research team member who is blind to allocation. Standard colonoscopic follow‐up will be collected by a colonoscopist not involved in the trial. Colonoscopists will collect mucosal biopsies and recurrence data, relative to the small bowel mesenteric tattoo. At the end of the study (12–57 months after surgery) further data will be collected by a team member who is blind to allocation.

Participants may withdraw their consent for the study at any time. Although the participant is not required to give a reason for discontinuing their study treatment, a reasonable effort will be made to establish this reason while fully respecting the participants’ rights.

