Secondary endpoints will be analysed as follows: Time‐to‐event outcomes will be analysed as per the primary outcome. Binary outcomes will be compared between the two factors ((1) Kono‐S vs. standard anastomosis and (2) extended vs. close mesenteric resection) using a multi‐level mixed effects logistic regression model with adjustment for baseline covariates, with associated ORs and 95% CIs. Absolute risk differences with 95% CIs will also be presented for binary outcomes. Continuous outcomes will be analysed using a multi‐level mixed effects regression model with adjustment for baseline covariates. All multi‐level models will use the same covariates as the primary analysis model. The serious adverse event (SAE) rates in the post‐randomisation period will be compared between the four randomised groups using a chi‐squared test and 95% CIs for each of the four randomised groups. We will also count the total number of SAEs experienced by each patient and compare counts using a Poisson generalised linear model (GLM) and reporting the risk ratio and associated 95% CIs.

Regardless of the statistical significance of the overall effect, exploratory subgroup analyses will be carried out for the primary outcome (ER). We will carry out subgroup analyses to examine if treatment effects differ based on patient demographics, disease phenotype and medical treatment history. As this trial is not formally powered for subgroup analyses, all subgroup effects will be considered exploratory, and *p*‐values will not be presented.

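### The ≥i2b and ≥i3 outcomes are worded as incidence at 3 years, but under even accrual about half the patients cannot have 3 years of follow-up, so a crude proportion or logistic analysis would not estimate that quantity efficiently or without bias

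*Protocol article*

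**What the plan says.** The Secondary outcomes section of the protocol article lists "Incidence of endoscopic recurrence with a Modified Rutgeerts score ≥i2b at 3 years" and "Incidence of severe endoscopic recurrence (Modified Rutgeerts score ≥i3) at 3 years". It also lists clinician- and patient-reported "symptomatic recurrence up to 3 years".

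Follow-up is described in several places:

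- The end of the Introduction describes a trial with 1 year of follow-up (−6/+3 months).
- Sample size: "All participants will be followed up for a minimum of 6 months", with a cap of 3 years.
- Data collection: "At the end of the study (12–57 months after surgery) further data will be collected".
- Table 1 has a last column headed "Study end (up to 5 years)". Colonoscopy is marked at 12 months (−6 to +3) and, by note review, at study end. CDAI and IBD-Control are marked at baseline, 6 weeks and 12 months only. There is no 3-year column.
- Recruitment runs "over a maximum of 45 months".

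Statistical methods offers two relevant routes for secondary outcomes. Time-to-event outcomes follow the primary Weibull model. For the rest, "Binary outcomes will be compared between the two factors" by mixed-effects logistic regression, with odds ratios and absolute risk differences. The article does not say which route the ≥i2b and ≥i3 outcomes take. The only censoring rule is the one for the primary outcome, recurrence at ≥i2.

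**The concern.** The primary outcome is worded as a time to recurrence. These two are worded as an incidence at a fixed time, so a reader would take them as yes/no outcomes for the logistic model. That model has no censoring. A patient last known to be free of ≥i3 recurrence at, say, 18 months has no observed 3-year status and must be counted as a non-event, dropped or imputed. If such patients are a large share of the trial, the published 3-year incidences and risk differences would depend on that choice.

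The primary outcome's censoring rule cannot simply be carried over either. A patient scored i2a has had the primary event but remains at risk of ≥i2b and ≥i3.

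**Working it through.** **1. The plan's own figures.** A 45-month recruitment maximum plus 12 months for the last patient gives 45 + 12 = 57, which matches the stated 12 to 57 months. Study end therefore behaves as a common calendar date, and follow-up length depends on entry date. The sample size is a separate matter and reproduces. HR = ln(0.675)/ln(0.475) = 0.528 gives 111 Freedman events (stated: 112). Dividing by 0.425, multiplying by a design effect of 1 + 14 × 0.01 = 1.14 and dividing by 0.97 gives 307 to 311 (stated: 308).

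**2. Who can reach 36 months.** Only patients entering by month 57 − 36 = 21 can.

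- Even accrual (assumed): 21/45 = 46.7%, about 144 of 308. The other 53.3%, about 164, cannot.
- Slower start (assumed): with a 12-month ramp 61.5% cannot; with a linear ramp throughout 78.2% cannot.
- Using the 6-month minimum from Sample size instead (range 6 to 51 months): 15/45 = 33.3% can, and 66.7%, about 205, cannot.
- Shorter even recruitment of R months, with study end still 12 months after the last entry: the share reaching 36 months is 1 − 24/R, which is below one half for every R up to 45.

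Only front-loaded accrual, with more than half the patients entered by month 21, would bring the unobservable share below half.

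**3. What a crude 3-year proportion would show.** The assumptions are constant hazard, perfect detection, even accrual, follow-up f of 12 to 57 months, and an illustrative 1-year risk. For a 10% risk at 1 year, λ = −ln(0.9)/12 = 0.00878 per month and the true 3-year incidence is 1 − 0.9³ = 27.1%.

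- Mean observed incidence among those with f below 36: 1 − (0.9 − 0.729)/(24λ) = 1 − 0.171/0.2107 = 18.85%.
- All patients kept, unobserved time counted as event-free: 0.467 × 27.1% + 0.533 × 18.85% = 22.7%.
- Early events kept, event-free patients with f below 36 dropped: 0.227/(0.467 + 0.533 × 0.1885) = 0.227/0.567 = 40.0%.

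| Handling | 10% at 1 year | 20% at 1 year |
|---|---|---|
| True 3-year incidence | 27.1% | 48.8% |
| Short follow-up counted as event-free | 22.7% | 41.7% |
| Event-free with short follow-up dropped | 40.0% | 63.6% |
| Only patients with 36 months (about 144) | 27.1% | 48.8% |

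With the 6 to 51 month range, the 10% column becomes 20.1% and 45.3% for the two biased handlings.

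**4. Detection.** Even for patients with 36 months, 3-year endoscopic status exists only if a routine colonoscopy was done and appears in the notes. The article gives no rate for this, so no figure is attached to it.

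**The case against.** The strongest reply is that the article never assigns these outcomes to the logistic model, and incidence at 3 years can equally mean a cumulative incidence from the survival route. An analysis plan not shown may say exactly that. This stands: a reader might infer that a logistic analysis is fixed, but the text only suggests it.

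A reader might also infer that the 3-year incidences will be understated. The documents do not support a direction, because no handling rule is given: one handling understates, one overstates, and restriction to 36 months introduces no follow-up bias but loses over half the sample. Nor can one say the figures would stay at their 12-month level, some 17 to 29 points low (27.1 − 10 and 48.8 − 20). That supposes note review finds nothing, whereas Table 1 plans to capture later colonoscopies that way.

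The treatment contrast is less exposed than the absolute figures. Randomisation within centre should balance follow-up length between groups. Treating the two columns above as two arms, the true odds ratio is 2.56 and the risk difference 21.7 points. Counting short follow-up as event-free gives 2.44 and 19.0 points. With good detection the comparison moves little.

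Most of the follow-up ranges can be reconciled: 12 months minus 6 gives the 6-month minimum, 57 months lies within 5 years, and 3 years is the analysis cap. The loose statement is the 1-year follow-up in the Introduction. Clinician-reported symptomatic recurrence can come from notes, so only the patient-reported part after 12 months lacks a listed source.

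What the objection does not remove is a stated fixed time point that about half the sample cannot reach, with no censoring rule for these grades.

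**Conclusion.** The point holds in a limited form. Two secondary outcomes are fixed at 3 years, no 3-year assessment is scheduled, and under even accrual over 45 months about 53% of patients (about 164 of 308) cannot have 36 months of follow-up; slower early recruitment raises that share. A crude proportion or logistic analysis would be biased, in a direction set by the handling, or would rest on under half the patients. The illustrative sizes (27.1% read as 22.7% or 40.0%) depend on the assumed 10% 1-year risk, constant hazard and perfect detection, none of which the article states.

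This is worth correcting before analysis because it changes what the 3-year figures mean. It concerns secondary outcomes only. The primary outcome already has a time-to-event analysis with censoring, and the sample size is untouched.

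**What to change.** - Define ≥i2b and ≥i3 recurrence to 3 years as time-to-event outcomes. Censor at the last colonoscopy known to be free of that grade, preferably with an interval-censored likelihood, since onset lies between examinations. Use the survival model already planned for the primary outcome.
- Report a model-based or non-parametric 3-year cumulative incidence, not a crude proportion.
- If a binary analysis is kept, tie it to the protocol colonoscopy (12 months, −6/+3) and label it so.
- Limit the patient-reported part of symptomatic recurrence to the visits that collect it, that is, to 12 months.
- Reconcile the 1-year follow-up in the Introduction with Secondary outcomes, Table 1, Sample size and Data collection.

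The cost is wording in the protocol and analysis plan, with no new visits. The downside is that a retained binary result becomes a 12-month quantity, and the 3-year estimate leans on earlier-recruited patients and on routine colonoscopies found in the notes. That dependence should be stated with the result.

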### Study setting

The study will recruit patients aged over 18 years undergoing ileocolic resection for primary/recurrent CD where an anastomosis is carried out. The study will be run nationally within the United Kingdom across up to 27 centres, recruiting an average of one participant per 4 months over a maximum of 45 months.

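### Recurrence ≥i2b and ≥i3 are defined as incidence at 3 years, a time point that about half the patients cannot reach and at which no colonoscopy is scheduled

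*Protocol article*

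**What the plan says.** All places are in the protocol article.

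- **Secondary outcomes** sets two endoscopic outcomes at a fixed time: "Incidence of endoscopic recurrence with a Modified Rutgeerts score ≥i2b at 3 years follow‐up" and "Incidence of severe endoscopic recurrence (Modified Rutgeerts score ≥i3) at 3 years follow‐up". The same list words other recurrence outcomes differently, for example "Surgical recurrence up to 3 years (clinician and patient reported". The primary outcome is likewise a time to event over up to 3 years.
- **Study setting** describes up to 27 centres "recruiting an average of one participant per 4 months over a maximum of 45 months".
- **Sample size**: "All participants will be followed up for a minimum of 6 months post‐randomisation and up to a maximum of 3 years".
- **Data collection**: "At the end of the study (12–57 months after surgery) further data will be collected".
- **Table 1** has one visit with colonoscopy, at 12 months (−6 to +3). The study-end column marks colonoscopy as obtained by note review.
- **Statistical methods** analyses time-to-event secondary outcomes like the primary one, a Weibull model with censoring. For the other main class, "Binary outcomes will be compared between the two factors" by mixed-effects logistic regression, with odds ratios and absolute risk differences. It does not say to which class the ≥i2b and ≥i3 outcomes belong.

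**The concern.** An incidence at 3 years needs each patient's status at 36 months, or a method that allows for patients not followed that long. The protocol's dates rule out the first for about half the sample. Its wording points away from the second, because a fixed-time incidence reads most naturally as a yes/no outcome, and the logistic model for such outcomes has no censoring.

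Under that reading, a patient last examined at month 14 without ≥i3 is either called free of severe recurrence at 3 years, which is not known, or left out. At stake are the reported 3-year incidences and risk differences for ileal (≥i2b) and severe (≥i3) recurrence. Clinicians would quote these as absolute figures, and they would depend partly on when recruitment happened.

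**Working it through.** **1. Do the dates fit together?** 27 centres × 45 months ÷ 4 months per patient = 303.75, close to the target of 308, so the full 45 months are needed. The study-end range agrees: 57 − 12 = 45 months.

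**2. Share able to reach 36 months.** Assume even accrual over 45 months.

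Share reaching 36 = (45 + minimum follow-up − 36) ÷ 45

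| Minimum follow-up | Reach 36 months | Cannot reach 36 months |
|---|---|---|
| 12 months (Data collection) | 21/45 = 46.7% | 53.3%; 308 × 0.533 = about 164 |
| 6 months (Sample size) | 15/45 = 33.3% | 66.7%; 308 × 0.667 = about 205 |

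Slow early recruitment makes this worse. With the 12-month minimum and a linear ramp-up over the first 6 or 12 months, 57% or 62% cannot reach 36 months.

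The Recruitment section gives a conflicting rate, "recruiting one participant per month over a maximum of 45 months". Read per centre, it gives 27 × 45 = 1,215 patients, or 308 in about 11 months. That fits neither the Study setting rate nor the 12 to 57 month range, so it is not used here.

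**3. Effect of counting short follow-up as no event.** The article gives no ≥i3 rates, so these inputs are assumptions: constant hazard, 3-year incidence of 30% in the control arm, and the hazard ratio implied by the design's ≥i2 rates, ln(1 − 0.325) ÷ ln(1 − 0.525) = 0.528. The other arm's 3-year incidence is then 1 − 0.70^0.528 = 17.2%.

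Observed proportion = average of 1 − exp(−h × min(f, 36)), with follow-up f uniform on 12 to 57 months and h = −ln(0.70)/36 = 0.0099 per month in the control arm.

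| | Control | Intervention | Risk difference | Odds ratio |
|---|---|---|---|---|
| Assumed truth at 3 years | 30.0% | 17.2% | 12.8 points | 2.07 |
| Short follow-up counted as no event | 25.2% | 14.3% | 10.9 points | 2.02 |

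The odds ratio is control against intervention, from unrounded values.

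Varying the assumed control incidence (same hazard ratio, 12-month minimum):

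| Assumed 3-year incidence | Proportion observed | True risk difference | Observed risk difference |
|---|---|---|---|
| 15% | 12.5% | 6.8 | 5.7 |
| 20% | 16.7% | 8.9 | 7.5 |
| 40% | 33.9% | 16.4 | 14.1 |

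Across this range, the control incidence is understated by about 2.5 to 6 points.

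**4. Effect of dropping them.** About 144 of 308 remain (308 × 21/45). Standard errors grow by about √(308/144) = 1.46. Even these 144 have a grade near 3 years only if a clinical colonoscopy was done then.

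**The case against.** **The outcomes are never called binary.** This stands. A 3-year cumulative incidence is an ordinary output of a censored survival model, and the article provides one for time-to-event secondary outcomes. The analysis plan, which is not shown, may put these outcomes there. The consequences in steps 3 and 4 are therefore conditional on the logistic model being used. What does not depend on it is that the stated time point cannot be observed for most patients and differs from the wording of the neighbouring outcomes.

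**Randomisation balances follow-up.** This also stands. Allocation is concurrent and stratified by centre, so follow-up length should be similar between arms. A reader might infer that the comparison between arms is biased; the documents do not support that, and the odds ratio barely changes.

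**The understatement could look far larger.** If only one colonoscopy between months 6 and 15 counted, the same assumptions would give about 10% vs 5% and a risk difference of 4.5 points. That is a bound, not an expectation, because Table 1 also collects later colonoscopies by note review. Even there the odds ratio is about 1.9.

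**Are these the only outcomes that separate ileal disease from lesions at the join?** A reader might think so, but the primary outcome carries an i2a/i2b subgroup analysis, and the Discussion repeats that stratification.

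**Conclusion.** The point holds as a mismatch between outcome definition and design. The two endoscopic outcomes name a 3-year time point that about 53% of patients cannot reach (67% on the 6-month minimum), and for which the schedule provides no colonoscopy. The 53% rests on even accrual over the full 45 months, which the Study setting rate supports.

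If the logistic model is applied, absolute incidences and risk differences come out too low when short follow-up is counted as no event, or about half the sample is lost when those patients are dropped. The 25% vs 14% illustration rests on an assumed ≥i3 incidence, a constant hazard, and a hazard ratio borrowed from ≥i2. The direction is firm; the size is not.

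The primary outcome, its censoring and its power are unaffected. This is a correction to secondary outcomes that should be settled before analysis; it does not threaten the trial's main conclusion.

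**What to change.** 1. In both definitions, replace the fixed 3-year point with follow-up up to 3 years, as for the primary outcome and the other recurrence outcomes.
2. State that both are analysed as time to first ≥i2b and time to first ≥i3, censored at the last date known to be free of that grade, with the same mixed-effects Weibull model as the primary outcome.
3. Take any 3-year cumulative incidence, and its difference between arms, from that model.
4. If a yes/no outcome is also wanted, define it at the scheduled 12-month (−6/+3) colonoscopy and keep the logistic model for it. I would not make it the headline, because that changes the question to recurrence at about 1 year. Nor would I adjust it for the timing of the colonoscopy, which is set after randomisation and may depend on symptoms.

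The cost is wording in the protocol and analysis plan, and in the registry entry if it carries the same text. No new data are needed. The small downside is that the 3-year incidence becomes model-based and rests on few late colonoscopies done for clinical reasons; the report should say so.

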There are commonalities with the techniques of Kono‐S anastomosis and extended mesenteric resection that may explain their potential effectiveness. Both isolate the anastomosis from the diseased mesentery. Kono‐S achieves this through a totally antimesenteric anastomosis placed as far away as possible from the mesentery, while extended mesenteric resection removes the theoretical disease driver. A combined approach is technically feasible and may improve efficacy. If either or both interventions result in reduced recurrence, understanding the underlying mechanism of action becomes a crucial question. To explore this, we will examine the locality of any mucosal recurrence. The prevailing notion is that CD arises from the interplay of genetically inheritable traits and environmental factors, including the microbiota, leading to innate and adaptive immune cell‐mediated inflammation [22]. Analysing the immune cell phenotypes in the mucosa of the different combinations of resection and anastomosis will provide insights into the impact each intervention has on the mechanism of inflammation [23, 24, 25]. Examining visceral fat area, anastomotic locality of immune cell populations, with a specific focus on T cell activation and exhaustion, will enable us to explore potential underlying mechanisms of action.

We propose a protocol for a UK multicentre, superiority, 2 × 2 factorial, randomised, open‐label trial with a 1‐year follow‐up (−6 months/+3 months). Participants will be randomised (1:1:1:1) to one of four groups:
Kono‐S + extended mesenteric resection;Kono‐S + close mesenteric resection;Standard anastomosis + extended mesenteric resection;Standard anastomosis + close mesenteric resection.

Our trial will investigate relevant clinical and mechanistic outcomes on: (1) the Kono‐S anastomosis; (2) extended mesenteric excision; (3) the locality of recurrence after surgery; and (4) local tissue immune response and its association with surgical recurrence.

The main aim of the study is to compare recurrence after standard mesenteric excision or extended excision and standard anastomosis or Kono‐S anastomosis (with or without extended mesenteric excision).

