### Mesenteric excision

#### Extended mesenteric excision

The mesentery is resected up to the origin of the ileocolic trunk but preserving the ileocolic vessels as described, in detail, in the SPICY trial [20, 26]. In participants who have markedly extensive inflammation affecting the vascular root of the mesentery seen on imaging or at operation, these should not undergo extended resection due to the risk of vascular injury and should be excluded from the trial.

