### Statistical methods

The primary outcome is the time to endoscopic recurrence (ER), over a follow‐up of up to 3 years, defined as a Modified Rutgeerts score [≥i2]. Patients without a reported ER will be censored at their last known date of not having had ER. The primary effectiveness analysis, on the intention‐to‐treat (ITT) sample, will compare the time to ER, between the two factors (Kono‐S vs. standard anastomosis surgery; extended mesenteric resection vs. close mesenteric resection) using a mixed‐effects parametric survival model with random effects for centre and surgeon and fixed effects for the two factors. The model will be implemented using a Weibull survival distribution.

It is anticipated that there will be no interaction between the two factors. To test this assumption, the initial statistical model will include an interaction (Kono‐S (yes or no) vs. extended mesenteric resection (yes or no)) term between the two factors. We will report the estimate of the interaction term and its associated 95% confidence interval (CI).

If the CI for the hazard ratios (HR) for the interaction term shows no evidence of an interaction, then we will analyse the data, without the interaction term, using the simpler factorial design with the two main factors. The CIs for the HRs for the Kono‐S versus standard anastomosis contrast and extended mesenteric resection versus close resection contrasts will be reported from this simpler model. If the CI for the HR for the interaction term demonstrates evidence of an interaction, then we will analyse the data using the four randomised groups separately, with standard anastomosis and close mesenteric resection as the reference treatment. The treatment effects and corresponding 95% CIs will be presented for all relevant comparisons.

We will complement the ITT analysis of the primary outcome with several sensitivity analyses. A per protocol analysis will estimate the efficacy of the Kono‐S versus standard anastomosis and extended versus close mesenteric resection in participants who adhere to the main aspects of the protocol. For participants who do not have a colonoscopy during the trial, or whose Modified Rutgeerts score was not completed, missing data will be imputed through best‐ and worst‐case scenarios to investigate the impact of assuming informative missingness (missing not at random assumptions).

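### Leak and the other binary complications are planned only as two marginal factor comparisons, so a leak risk specific to Kono-S plus extended excision could not be isolated and would be attributed to each technique alone

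*Protocol article*

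**What the plan says.** Under Secondary outcomes, the protocol article names "Radiological and surgical anastomotic leak as defined by the latest consensus [33]; other complications for each intervention assessed at the time of surgery", and continues to 6 weeks and 12 months. Leak is a yes/no outcome, and complications become one when counted as any versus none.

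Statistical methods then treats the types of outcome differently:

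- **Primary outcome:** "the initial statistical model will include an interaction". If the confidence interval shows evidence of interaction, "then we will analyse the data using the four randomised groups separately".
- **Time-to-event secondary outcomes:** these "will be analysed as per the primary outcome", so the interaction step goes with them.
- **Binary secondary outcomes:** "Binary outcomes will be compared between the two factors", namely Kono-S versus standard anastomosis and extended versus close excision, by mixed-effects logistic regression with odds ratios and absolute risk differences. No interaction term and no four-group presentation is stated.
- **Serious adverse events:** rates are compared across the four randomised groups by a chi-squared test, with a 95% CI for each group.

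The section adds that the multi-level "models will use the same covariates as the primary analysis model". That does not settle whether the interaction step applies to binary outcomes.

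**The concern.** The combined operation is a treatment of interest in its own right. The Introduction says of it: "A combined approach is technically feasible and may improve efficacy". The Discussion promises to assess the two techniques singly and together. For efficacy, the plan expects no interaction but checks for one. For leak and the other binary complications, it relies on the same expectation and states no check.

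A two-factor model without an interaction term has one effect for each technique. It cannot represent an excess that appears only when both are used, so it spreads that excess over both. A reader of the trial report could then conclude that Kono-S alone, and extended excision alone, each raise the odds of leak when neither does. The stated analysis would show nothing to correct that reading.

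**Working it through.** **Group sizes.** The target is 308, randomised 1:1:1:1, so 308/4 = 77 per group and 308/2 = 154 per level of each factor. The 154 matches the Sample size section. The stated size itself reproduces closely:

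- HR = ln(1 − 0.325)/ln(1 − 0.525) = 0.528.
- Freedman's formula gives 111 events, or 112 with the HR rounded to 0.53.
- 112/0.425 × 1.14/0.97 = 309.7, against 308 stated. Here 0.425 is the mean of 52.5% and 32.5%, and 1.14 = 1 + 14 × 0.01.

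**Assumptions for leak.** The documents give no leak rate. I take a base rate p0 in three groups (3% or 5%) and a rate p1 in Kono-S plus extended only (10% or 15%). Clustering and attrition are ignored.

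**What the two-factor model estimates.** Write a for the fitted rate in the combined group, b for each single-technique group and c for standard plus close. Maximum likelihood makes the fitted margins equal the observed ones:

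- a + b = p1 + p0
- b + c = 2·p0
- odds(a)/odds(b) = odds(b)/odds(c) = OR for each technique

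For p0 = 5% and p1 = 15%, a + b = 0.20 and b + c = 0.10. The solution is b = 0.0672, a = 0.1328, c = 0.0328. The odds are 0.1531, 0.0720 and 0.0339, and each ratio is 2.13. The true odds ratio for either technique alone is odds(5%)/odds(5%) = 1.0.

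| Base rate / combined rate | Fitted OR, each technique (true alone: 1.0) | Marginal risk difference, each factor | Combined vs standard + close: true risk difference | same contrast: implied OR (fitted OR squared) | same contrast: true OR |
|---|---|---|---|---|---|
| 5% / 10% | 1.54 | 2.5 points | 5 points | 2.4 | 2.1 |
| 5% / 15% | 2.13 | 5 points | 10 points | 4.5 | 3.35 |
| 3% / 10% | 2.26 | 3.5 points | 7 points | 5.1 | 3.6 |
| 3% / 15% | 3.25 | 6 points | 12 points | 10.6 | 5.7 |

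The implied risk difference for the combination is a − c = (a + b) − (b + c) = p1 − p0, which is the true one. At 5%/15% it is 13.3% − 3.3% = 10.0 points. The error therefore lies in the attribution to single techniques: each single-technique group is fitted at 6.7% when its true rate is 5%.

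**What an interaction test could do.** At 5%/15% the interaction OR is 3.35. Its log is 1.210 and the standard error is 0.960, so power is Φ(1.210/0.960 − 1.96) = Φ(−0.70), about 24%. The 95% CI spans a factor of exp(1.96 × 0.960), about 6.6, either way. For combined-group rates of 10% to 20% with 5% elsewhere, power is 12% to 38%.

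**What the direct contrast could do.** At 5%/15% with 77 versus 77, the standard error of the risk difference is √[(0.05 × 0.95 + 0.15 × 0.85)/77] = 0.048. The 95% CI is about ±9.3 points and power is about 54%. Each marginal contrast (10% versus 5%, 154 versus 154) has power of about 38%.

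**The case against.** **Two-factor contrasts are the usual factorial analysis, and a four-group table may be in the analysis plan.** Both are fair. The article does not say that the two contrasts are the only output, and the analysis plan is not shown. But the article is not silent here. It states a rule for binary outcomes, and in the same section gives the primary outcome, the time-to-event secondaries and the serious adverse events some route to the four groups. The stated rule is what needs the addition.

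**Serious adverse events are already compared by group.** This stands in part. The per-group CIs would include leaks that qualify as serious, and the data monitoring committee sees safety data every 6 months. But the comparison pools all event types, and the leak outcome includes radiological leaks, not all of which need be serious adverse events.

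**The marginal risk difference is not wrong.** Correct. Five points at 5%/15% is the proper average effect of one factor over both levels of the other. It is simply not the effect of either technique alone.

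**Stronger readings that the documents do not support.** A reader might infer that the model understates the risk of the combination. It does not in general: the implied risk difference against standard plus close is exact in these scenarios and the implied odds ratio is too high (4.5 against 3.35). Only the fitted absolute rate is low, at 13.3% against 15%. Nor are the results wrong for just some of the operations; at 5%/15% all four fitted rates are off by about 1.7 points.

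A reader might also take the remark that some patients "should not undergo extended resection due to the risk of vascular injury" as evidence that leak would concentrate in the combined group. That remark concerns marked inflammation at the vascular root, which is an exclusion criterion. The Introduction's end-artery account concerns recurrence at the mesenteric border, whereas Kono-S is antimesenteric. The documents offer no evidence of a leak interaction.

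**Conclusion.** The point holds in a limited form. For leak and the other binary complications, the stated analysis cannot isolate a risk specific to the combined operation, and would assign such a risk to each technique alone. The spurious odds ratio is about 1.5 to 3.3 against a true 1.0. This rests on assumed leak rates, on 77 per group, and on an excess confined entirely to one group. Whether such an excess exists is unknown. The case for change is that the plan undertakes to assess the combination, checks interaction for efficacy and not for these harms, and could close the gap with data it already collects. It does not bear on the primary analysis or the sample size.

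**What to change.** Keep the two marginal odds ratios and risk differences. For anastomotic leak and the other binary complications, add to Statistical methods that the following will be reported regardless of any test:

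1. the number and rate, with 95% CI, in each of the four randomised groups;
2. the risk difference, with 95% CI, for Kono-S plus extended versus standard plus close;
3. the interaction estimate with its 95% CI, labelled descriptive and not used as a gate, because its power is low.

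State that safety conclusions about the combined operation rest on the four-group figures in items 1 and 2.

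The cost is one table and a sentence or two of wording, with no new data. The drawback is imprecision at about 77 per group: a 5% rate means about four events (0.05 × 77 = 3.85), so the intervals will be wide and should be read as such.
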